## Methods/design

### Study design

The SWIVIT trial is a prospective, patient-blinded, multicenter, randomized controlled trial at the anesthesia departments of the University Hospital of Bern, the University Hospital of Lausanne and the University Hospital of Geneva, all in Switzerland.

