### Sample size calculation

Most previous studies have based sample size calculations on differences of the intubation difficulty score (IDS), developed by Adnet in 1997 for direct laryngoscopy [12]. However, a retrospective study by McElwain has raised concerns about the validity of the IDS with VLS [13]. The most important outcome parameter for VLS or any guided intubation devices is the success rate. Most available data are from patients with normal airway anatomy and, therefore, not comparable with our setting. Only one study immobilized the patients’ necks with collars to investigate the C-MAC in 43 patients. That study found an overall success rate of 88% [10]. This is an unacceptable low success rate for the management of a difficult airway, but the study was underpowered: we calculated the 95% CI in that study to be 0.75 to 0.95 for overall success rate.

In order to rate an intubation device as “successful”, we define that the lower limit of the 95% CI should not be smaller than 0.9. We based our sample size on these values, congruent with our findings in a small pilot sample. We calculated the necessary sample size to obtain a distance of 0.05 to the expected success rate of 0.95, provided a probability of 0.95 and a power of 80% (SAS v.9.1, SAS Institute Inc., Cary, NC, USA). A total of 107 patients per device are necessary for this lower limit of 0.9. A total of 642 (6 × 107) patients will be necessary based on these assumptions, which leads us to include 720 patients to compensate for dropouts or missing data.

Secondary endpoints include parametric data, such as time necessary until success. Time until success has varied widely among different devices in published studies. Furthermore, that parameter seems to be influenced by the anesthesia provider. Therefore, we based our sample size calculation on first attempt success rate.

Because available data about our primary outcome, the first attempt success rate in a simulated difficult airway scenario, are scarce, we will recalculate sample size after the first 120 patients, based upon the values obtained from the first 20 patients for each device. In order to reduce bias, all participating investigators will remain unaware of results obtained from these 120 patients.

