#### Allocation of patients

Patients with written informed consent are randomly allocated to one of the six devices. The allocation sequence will be generated using online randomization software (http://randomization.com) in blocks of 30 intubations for the devices and stratified for each participating center and for each physician. The allocation will be concealed in sealed, opaque, sequentially numbered envelopes and will not be opened until the patient is anesthetized.

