#### Clinical study procedure

Premedication will be according to the standard operating procedures of the participating centers. Standard non-invasive monitoring includes ECG, non-invasive arterial blood pressure, oxygen saturation (SpO_2_), end-tidal CO_2_ and volatile anesthetic level if applicable. A bispectral index (BIS, Aspect Medical Systems, Norwood, MA, USA) or a different processed EEG monitoring will be used whenever available. Anesthesia will be induced with propofol 1.5 to 3 mg/kg body weight and fentanyl 1 to 2 mcg/kg body weight. After facemask ventilation is established, neuromuscular blocking agents (rocuronium 0.6 mg/kg body weight) will be given and appropriate action monitored by neuro-stimulation. The inter-incisor distance at maximum mouth opening will be measured while the patient is asleep. Then, the extrication collar (Stifneck™, Laerdal, Copenhagen, Denmark) will be properly adjusted, and a self-adhesive tape will be used to fix the head on the operating table, as done in an earlier study by our group [6]. The inter-incisor distance will be measured at maximal mouth opening aiming at a mouth opening between 20 to 25 mm.

If mask ventilation remains adequate and a sufficient level of anesthesia is confirmed (BIS <55, stable hemodynamic parameters, unresponsiveness to jaw thrust), the tracheal intubation will be performed with the help of one of the six VLS, according to randomization.

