#### Definition of time

Time necessary until success is measured from the time the facemask is taken away from the face until the end-tidal CO_2_ curve appears on the monitor of the respirator. Time for each attempt is measured separately.

Cormack-Lehane (CL) grade [14] at laryngoscopy (not developed for indirect laryngoscopy, but necessary for the calculation of the IDS).

Inter-incisor distance before induction of anesthesia and after placement of the collar to measure maximum mouth opening and the reduction of mouth opening by the collar (collar adjusted to permit a minimal opening of 18 mm, according to the minimal requirements for Airtraq and King Vision)

Number of optimization maneuvers required (cricoid pressure or BURP, backward, upward, rightward pressure), second assistant, adjustment of head positioning) to aid tracheal intubation [15].

View on the glottic opening in percent (%) as judged by the operator: Percentage of Glottic Opening (POGO) Score [16].

Adverse events: cardiovascular extremes: any hypo-/ hypertension and tachycardia/ bradycardia exceeding 20% from baseline. Blood on device, and injury during intubation attempt, suspicion of aspiration/regurgitation (gastric fluid in the ventilation tube or in the hypopharynx), hypoxia (SpO_2_ <90%), bronchospasm, airway obstruction or any other form of stridor, coughing, dental, tongue or lip trauma.

Technical problems with the device, such as fogging, impeded vision and monitor/light source failure.

The Intubation Difficulty Scale (IDS) score will be calculated as previously published [12], using the following parameters: number of attempts and operators, alternative techniques, Cormack-Lehane grade, lifting force, laryngeal pressure and vocal cord mobility.

Demographic and perioperative data: sex, age, weight and body mass index, dentition, surgical procedure/ duration, duration of anesthesia, date/ time of hospital discharge.

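### The opening rule lets the team learn the device before fitting the collar and before the check that decides whether to proceed

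*Protocol article*

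**What the plan says.** Allocation of patients gives the only rule on timing: the allocation "will be concealed in sealed, opaque, sequentially numbered envelopes and will not be opened until the patient is anesthetized".

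Clinical study procedure gives the order of events. After induction, mask ventilation and neuromuscular block, "The inter-incisor distance at maximum mouth opening will be measured while the patient is asleep". The next step is the collar: "Then, the extrication collar (Stifneck™, Laerdal, Copenhagen, Denmark) will be properly adjusted". The head is taped and mouth opening is measured again, "aiming at a mouth opening between 20 to 25 mm". Intubation with the randomized device follows only on a condition: "If mask ventilation remains adequate and a sufficient level of anesthesia is confirmed".

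The list of measurements (under Definition of time) adds a floor for the setting: "collar adjusted to permit a minimal opening of 18 mm, according to the minimal requirements for Airtraq and King Vision".

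On blinding, Study design describes a "prospective, patient-blinded, multicenter, randomized controlled trial at the anesthesia departments". The section on postoperative evaluation also blinds the recovery-room and day-one assessors. Neither section mentions the operator or the person who fits the collar.

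**The concern.** The collar and tape create the difficult airway, so they set the difficulty that each device faces. The 90% benchmark and the guided-versus-unguided comparisons both rely on that difficulty being the same across arms. If the device is known while the collar is being adjusted, a more or less generous fit within the aimed range can follow the allocation, even unintentionally.

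The check before intubation has the same weakness. If the envelope is already open, a decision not to proceed concerns a patient whose device is known. Any such patient left out of the analysis would then be lost after allocation, possibly in a way that depends on the device.

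Concealment at enrolment is not in question. Consent is taken the day before surgery and the envelopes are sealed, opaque and numbered. The exposure lies between induction and the first attempt.

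**Working it through.** The protocol states no figure on this point, so the main check is the order of steps.

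**Sequence (Clinical study procedure) against the opening rule (Allocation of patients)**

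| Step | Opening permitted by the rule? |
|---|---|
| Consent, day before surgery | No |
| Induction, mask ventilation, neuromuscular block | From the point at which the patient counts as anesthetized |
| Mouth opening measured in the sleeping patient | Yes |
| Collar adjusted, head taped | Yes |
| Mouth opening measured again, aim 20 to 25 mm | Yes |
| Mask ventilation and depth of anesthesia checked | Yes |
| Intubation with the allocated device | Device must be known |

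The condition for opening is met before both steps at which knowledge of the device could matter. No other section shown moves the opening later.

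**Illustration 1: sensitivity of the benchmark to a shift in true success.** The size of the shift is assumed; the documents do not link collar fit to success.

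Inputs: 720/6 = 120 patients per device. A device passes if its lower 95% limit is at least 0.9 (Sample size calculation). The Wilson interval is my choice, because the article does not name a method. The Wilson lower limit, with p = x/n and z = 1.96, is

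[p + z²/(2n) − z·√(p(1−p)/n + z²/(4n²))] / (1 + z²/n).

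- x = 114: lower limit 0.895, fails.
- x = 115: lower limit 0.906, passes.

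The pass probability is therefore P(X ≥ 115) for X binomial with n = 120:

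| Setting | Successes needed | True 0.92 | True 0.95 | True 0.97 |
|---|---|---|---|---|
| n = 120, Wilson | 115 | 0.075 | 0.442 | 0.847 |
| n = 107, Wilson | 103 | 0.064 | 0.376 | 0.781 |
| n = 120, Wald | 114 | 0.147 | 0.606 | 0.930 |

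In the first row, going from 0.92 to 0.95 (3 points) changes the probability by 0.442 − 0.075 = 0.367. Going from 0.95 to 0.97 (2 points) changes it by 0.847 − 0.442 = 0.405. Across the three rows, these changes run from 0.312 to 0.460.

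**Illustration 2: losses after opening.** The sample size section says "which leads us to include 720 patients to compensate for dropouts or missing data". The allowance is 720 − 642 = 78 patients, or 78/6 = 13 per device (78/720 = 10.8%). Assume true success of 0.90 in 120 patients (108 successes), with some patients stopped at the check and left out:

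- 3 lost, all of whom would have failed: 108/117 = 0.923.
- 3 lost, with success 0.5 among them: (108 − 1.5)/117 = 0.910.
- 6 lost, all of whom would have failed: 108/114 = 0.947.
- 6 lost, with success 0.5 among them: (108 − 3)/114 = 0.921.

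Losses well inside the allowance could thus move an observed rate from 0.90 towards the assumed 0.95. Even the most extreme of these cases does not pass by itself, since the Wilson lower limit at 108/114 is 0.890.

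**The case against.** The strongest reply is that the rule is a lower bound and instructs nobody to open early. Clinical study procedure mentions randomization only at the end of its sequence, and it confirms a sufficient level of anesthesia after the collar is on. The word anesthetized could mean that later point. The study flow chart (Figure 2) is not shown and may fix the order, and an article condenses its full protocol. This stands to the extent that early opening is permitted, not certain. It does not remove the point: the same section already describes the patient as asleep before the collar, so the wording is at best ambiguous, and nothing shown rules out early opening.

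There are partial safeguards. Mouth opening is measured before and after the collar against a numeric aim, so uneven fitting would be partly visible by arm. That detects an imbalance but does not prevent it, and it captures only one aspect of difficulty. Stratification by physician balances stable differences between operators, not knowledge of the device. No study device has entered the mouth when mask ventilation is checked, so only judgement could make stopping depend on the device, and parts of the check have stated criteria.

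Three stronger readings are tempting but unsupported:

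- **That the two mouth-opening statements conflict.** They do not. Every value from 20 to 25 mm satisfies an 18 mm minimum. The minimum is explained by the needs of two devices but is not restricted to their arms, which suggests a common setting. At most, the handling of an opening between 18 and 20 mm could be clarified.
- **That patients who fail the check are excluded after randomization.** The article sets a condition for proceeding. It does not say what happens to those who fail it, or whether their envelope is open by then.
- **That the change in pass probability measures this defect.** It shows how steep the pass rule is near the benchmark. Any cause of a 2 to 3 point shift would produce it.

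**Conclusion.** The point holds as a weakness in the written timing rule. As worded, the rule allows a team not described as blinded to know the device while it sets the difficulty of the airway and decides whether to go on. The conclusion rests on reading anesthetized as satisfied once the patient is asleep, and on no undisclosed document setting a later time. Whether bias would follow, and how large it would be, cannot be determined from the documents. The pass probabilities and loss scenarios rest on assumed shifts and losses and are illustrations only. The change is worth making because it closes a route to bias in the primary outcome at almost no cost. It is not evidence that the results would be wrong.

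**What to change.** Replace the timing rule in Allocation of patients with one stating that the envelope is opened only after three things: the collar and tape are in place, the inter-incisor distance with the collar has been recorded, and the protocol's existing check of mask ventilation and depth of anesthesia has been passed. Add that the patient counts as randomized at that moment, that a patient stopped before it uses no envelope, and that every patient whose envelope is opened is analysed in the allocated arm. Report mouth opening with the collar by device as a check on uniformity. If useful, clarify how an opening of 18 to 20 mm is treated.

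The cost is a few sentences, plus either a short delay while the device is handed over or having all six devices ready in the room. Trial status reports fewer than 10 patients enrolled, so a change at that stage would cover nearly the whole trial.

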#### Clinical study procedure

Premedication will be according to the standard operating procedures of the participating centers. Standard non-invasive monitoring includes ECG, non-invasive arterial blood pressure, oxygen saturation (SpO_2_), end-tidal CO_2_ and volatile anesthetic level if applicable. A bispectral index (BIS, Aspect Medical Systems, Norwood, MA, USA) or a different processed EEG monitoring will be used whenever available. Anesthesia will be induced with propofol 1.5 to 3 mg/kg body weight and fentanyl 1 to 2 mcg/kg body weight. After facemask ventilation is established, neuromuscular blocking agents (rocuronium 0.6 mg/kg body weight) will be given and appropriate action monitored by neuro-stimulation. The inter-incisor distance at maximum mouth opening will be measured while the patient is asleep. Then, the extrication collar (Stifneck™, Laerdal, Copenhagen, Denmark) will be properly adjusted, and a self-adhesive tape will be used to fix the head on the operating table, as done in an earlier study by our group [6]. The inter-incisor distance will be measured at maximal mouth opening aiming at a mouth opening between 20 to 25 mm.

If mask ventilation remains adequate and a sufficient level of anesthesia is confirmed (BIS <55, stable hemodynamic parameters, unresponsiveness to jaw thrust), the tracheal intubation will be performed with the help of one of the six VLS, according to randomization.

#### Selection of tracheal tube size (Mallinckrodt Hi-Contour Oral/Nasal Tracheal Tube Cuffed, Covidien, Hazelwood, MO, USA)

Women: 6.5 mm ID (internal diameter)

Men: 7.5 mm ID

#### Selection of blade size

1) Airtraq: Size #2 in women (6.5 mm tracheal tube does not fit in size #3 device), size #3 in men

2) A. P. Advance: Difficult airway blade for guided intubation

3) C-MAC: D-blade. Additionally, a pre-shaped stylet (shaped according to the decision of the consultant anesthesiologist) will be used for tracheal insertion.

4) GlideScope: GVL single use blade #3 with reusable GlideScope stylet for tracheal tube

5) King Vision: Blade #3 (channeled)

6) McGrath MAC: Disposable McGrath MAC blade. Additionally, a pre-shaped stylet (shaped according to the decision of the consultant anesthesiologist) will be used for tracheal insertion.

The primary endpoint is successful tracheal intubation confirmed by capnography (CO_2_ monitoring). Further management of anesthesia is according to the consultant anesthesiologist.

#### Device failure

A device failure is defined as two unsuccessful intubation attempts with a maximum of 180 seconds for each attempt while oxygen saturation remains >90%. The intubation attempt is allowed to continue if the laryngeal opening is identified after 180 seconds and the patient does not desaturate (SpO_2_ >90%). However, this will not count as success at the first attempt, but as an overall attempt success. After the second unsuccessful attempt, a third and last attempt will be performed with another device, chosen according to the decision of the attending anesthesiologist with the rigid collar in place. In case of failure of the second device, further airway management will be according to the decision of the attending anesthesiologist, and without the rigid collar.

#### Break-up criteria (leading to removal of the rigid collar)

Primary and secondary VLS device failure

Bronchospasm, injury

Technical failure of the intubation devices during insertion attempt (for example, light bulb failure or monitor failure)

If a break-up criterion is reached, the extrication collar will be removed, the patient ventilated if necessary and the trachea will be intubated via either the randomized device (one attempt) or any other further airway management device, according to the attending anesthesiologist. The attending anesthesiologist may choose another airway management strategy once a break-up criterion is reached.

#### Measurements

Insertion success (first and second attempt success rate).

#### Definition of success

Lung ventilation through the cuffed tracheal tube, confirmed by end-tidal CO_2_.

Time necessary for completion of the first attempt intubation, second attempt (if applicable) and overall intubation (calculated as the sum of the first and, if applicable, second attempt).

#### Definition of time

Time necessary until success is measured from the time the facemask is taken away from the face until the end-tidal CO_2_ curve appears on the monitor of the respirator. Time for each attempt is measured separately.

Cormack-Lehane (CL) grade [14] at laryngoscopy (not developed for indirect laryngoscopy, but necessary for the calculation of the IDS).

Inter-incisor distance before induction of anesthesia and after placement of the collar to measure maximum mouth opening and the reduction of mouth opening by the collar (collar adjusted to permit a minimal opening of 18 mm, according to the minimal requirements for Airtraq and King Vision)

Number of optimization maneuvers required (cricoid pressure or BURP, backward, upward, rightward pressure), second assistant, adjustment of head positioning) to aid tracheal intubation [15].

View on the glottic opening in percent (%) as judged by the operator: Percentage of Glottic Opening (POGO) Score [16].

Adverse events: cardiovascular extremes: any hypo-/ hypertension and tachycardia/ bradycardia exceeding 20% from baseline. Blood on device, and injury during intubation attempt, suspicion of aspiration/regurgitation (gastric fluid in the ventilation tube or in the hypopharynx), hypoxia (SpO_2_ <90%), bronchospasm, airway obstruction or any other form of stridor, coughing, dental, tongue or lip trauma.

Technical problems with the device, such as fogging, impeded vision and monitor/light source failure.

The Intubation Difficulty Scale (IDS) score will be calculated as previously published [12], using the following parameters: number of attempts and operators, alternative techniques, Cormack-Lehane grade, lifting force, laryngeal pressure and vocal cord mobility.

Demographic and perioperative data: sex, age, weight and body mass index, dentition, surgical procedure/ duration, duration of anesthesia, date/ time of hospital discharge.

#### Postoperative evaluation by blinded personnel

After anesthesia, the recovery room nurse (blinded about randomization) will use a checklist to assess for any airway trauma. The checklist, which includes questions about active oral bleeding, coughing blood, blood-stained saliva, sore throat, pain when swallowing, coughing, postoperative nausea and hoarseness, follows a 3-graded assessment by the patient (mild, moderate, severe). Timing of this assessment will be standardized to one hour after post-anesthesia care unit admission. If patients are extubated in the intensive care unit (ICU), the ICU nurse will make the assessments. On postoperative day one, a member of the study personnel will make a further assessment, using the same checklist. In case of ambulatory surgery, assessment will be done by telephone. The investigator will be unaware of the randomization, any problems encountered during intubation or surgery, and will be blinded about the performance of the airway device.

#### Data collection techniques

All clinical data will be collected by a research assistant at bedside, using digital data recording devices (tablets). In case of device failure, a back-up paper form will be available. All data will be sent to a secure, central data storage immediately after the closure of the local case report form.

#### Ethical approval

The SWIVIT randomized controlled trial has been approved by the ethic committee of the canton of Bern (KEK Bern ref. nr. 106/12 on 11 September 2012).

A summarizing study flow chart is provided in Figure 2.

**Figure 2 F2:**
[figure not shown]
Study flow chart.

## Discussion

According to the latest national audit in anesthesia in the UK, major adverse events are estimated to be as high as 1 in 5,500 anesthesia cases, leading to brain damage and even death [1]. Airway management was deemed to be good in only 19% of these cases. This is an unacceptable high failure rate for our patients’ safety. Therefore, new and supposedly better devices to manage the difficult airway are necessary and continue to enter the market, often without thorough evaluation of their efficacy. In case of use of such devices in a difficult airway situation, it is vital to know which device will perform best. While VLS are marketed to facilitate the tracheal intubation in difficult airway management, there are no adequately powered data available comparing VLS in real difficult airway situations or, at least, adequately simulated difficult airway models. We intend to deliver this evidence. This will be for the benefit and safety of patients presenting with an expected or unexpected difficult airway needing general anesthesia for surgery or interventions.

